### Pre- and postoperative assessment and data collection

At study inclusion, a primary treatment plan must have been decided upon, based on information obtained from findings at mammography, ultrasound, and core biopsy/cytology, according to current clinical standards. (Additional file 3). This plan may be subject to change after the clinical examination at the appointment when the diagnosis is given to the patient, as a result of findings of a larger or smaller tumor size in relation to breast volume, or due to comorbidity that may contraindicate a certain treatment. Any changes in the primary treatment plan after clinical examination must be clearly documented and motivated before CEM. (Additional file 5).

At the CEM examination, suspicious malignant findings will be noted according to a predefined protocol and if malignant-suspicious areas not previously located are identified by CEM they will be subjected to US-guided biopsy. The results of CEM will then be discussed at a second MDT conference, and taken into consideration in the primary treatment plan. (Additional file 8).

The whole study population will answer a short study-specific questionnaire including questions regarding possible allergy to iodinated contrast agent, weight and height, pre- or post menopausality, use of oral contraceptives, hormone replacement therapy or endocrine treatment after breast cancer, on-going pregnancy or breast-feeding, other diseases, previous surgery or radiotherapy to the breasts, and breast implants. This questionnaire will be administered at the appointment when the patient is informed about the study. Patients will also answer the preoperative version of the Breast-Q™ questionnaires [23]. These are globally used and validated patient-reported outcome measures. The Breast-Q™ questionnaires are currently the only validated, disease-specific questionnaires designed to evaluate different aspects of health-related quality of life and patient satisfaction related to breast cancer surgery.

The renal function of patients will be checked (normal range of serum creatinine 45–90 μmol/l) before the study inclusion, as the iodinated contrast agent may affect renal function.

A study-specific predefined imaging reporting protocol will be used for all imaging methods (DM, US and CEM), to assess morphological changes (solid tumors and/or micro calcifications), location of the lesions, size of each lesion and total extent of the malignant area (Additional files 1, 2, 6 and 7). The estimates of size will then be compared with the results from histopathological examination, which is considered to be the reference standard. Mammographic breast density will be evaluated according to the classification of American College of Radiation, Breast Imaging Reporting and Data System, 5th Edition (ACR BI-RADS) [24]. Background parenchymal enhancement on CEM will be classified as minimal, mild, moderate and marked. Findings will be classified as mass/lesion (visible on at least two views) or non-mass enhancement in as focal, linear, segmental regional, multiple regions, diffuse. Visual assessment of level of CEM enhancement in lesion/area will be reported as mild, moderate or marked. Classification of background parenchymal enhancement, findings and level of enhancement are described for MRI in ACR BI-RADS 5th edition [24], and will in this study be adapted for CEM, as suggested by Lobbes et al. [25]. Breast volume will be calculated from mammography images from measurements of width, *w*, and height, *h*, from the cranio-caudal projection of the mammogram, together with the compression, *c* (thickness of the breast when compressed during mammography), defining the breast as a half-elliptical cylinder, using the equation: $$ volume\ \left({cm}^3\right)=\raisebox{1ex}{$\pi $}\!\left/ \!\raisebox{-1ex}{$4$}\right.\times whc $$
*(cm)* [26, 27]. (Additional file 4). A software will also be used to calculate breast density and volume, for example Libra or Volpara™.

Information will be obtained from the histopathological report on the total tumor extent, the size of each tumor if multiple tumors, the type of cancer (ductal, lobular, other), uni−/multifocality, ductal carcinoma in situ (DCIS) / pleomorphic lobular carcinoma in situ (LCIS), histological grade, biomarkers: estrogen receptor, progesterone receptor, Her-2 status and Ki67. The total tumor extent will be given including and excluding classic LCIS (LCIS-C) when present. LCIS-C does not affect treatment and is usually not visible at imaging. Data on adverse events related to CEM, e.g. the use of the iodinated contrast agent, will be collected directly after the examination and recorded. (Additional file 9).

The CEM examinations will be performed using a Senographe Pristina™ mammography system equipped with the software SenoBright™ HD for CEM (*GE Healthcare*). The CEM images will be read by at least two experienced radiologists in consensus, and with access to the images and results of routine clinical imaging. If additional tumors are found compared to the initial routine clinical imaging, a second-look US examination will be performed.

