### Results of the feasibility study

In preparation for this prospective randomized trial, a feasibility study was conducted in 47 patients at the Unilabs Breast Centre, Skåne University Hospital in Lund [22]. The primary treatment plan was changed in 10/47 cases (21%): mastectomy instead of partial mastectomy due to multifocal cancer in three patients and due to larger unifocal extent in two patients; partial mastectomy instead of mastectomy due to improved demarcation of the tumor in one patient; bilateral surgery due to findings of contralateral cancer in two patients; and neoadjuvant treatment instead of primary surgery in two patients. Agreement with histopathological findings regarding preoperative estimation of the size of the malignant changes was better with CEM (Bland Altman statistics: mean difference − 1.36, SD ± 18.45) than with mammography (− 4.18, SD ± 26.20) and ultrasound (− 8.36, SD ± 24.30). No difference was found in the added value of CEM with age, breast density, type of cancer or the presence of micro calcifications.

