#### Secondary endpoints

Do preoperative CEM findings affect the frequency of reoperation or the number of pathologically avoidable mastectomies?Does preoperative CEM show better accuracy in tumor size estimation than mammography and ultrasound, in comparison with histopathological examination?Do other factors such as age, postmenopausality, breast density, type of cancer, or the presence of micro calcifications influence the added value of CEM regarding changes in the treatment plan and tumor size estimation?Is there a difference in health-related quality of life between patients that have undergone preoperative CEM and those who have not?What are the costs and benefits of additional CEM in a health-economic perspective?Does preoperative CEM affect the number of loco regional recurrences/ipsilateral new cancers or contralateral cancer within 5 years?

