#### Statistical analyses

Descriptive statistics for parametric variables will be expressed as the median, interquartile range and range. Descriptive statistics for non-parametric variables will be presented as frequencies and percentages. Fisher’s exact test will be used to identify differences between groups and subgroups when applicable.

Pearson’s correlation coefficient and Bland–Altman statistics will be used for each modality regarding preoperative size estimation of the malignant changes compared with histopathological examination. Mean and median values of the largest individual lesion and the total extent will be presented. A separate analysis will be carried out for an extent maximum of 5 cm due to the limitations in assessment by US due to the size of the probe.

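### The size-accuracy endpoint compares CEM with mammography and ultrasound, but the CEM size is recorded by readers who can see both, so the result does not isolate CEM

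*Protocol article*

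**What the plan says.** Under Secondary endpoints the protocol article asks: "Does preoperative CEM show better accuracy in tumor size estimation than mammography and ultrasound, in comparison with histopathological examination". Under Statistical analyses, Pearson's correlation and Bland–Altman statistics are to be used "for each modality regarding preoperative size estimation of the malignant changes compared with histopathological examination".

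The section Pre- and postoperative assessment and data collection supplies the data for this:

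- Mammography, ultrasound and CEM each have a structured report that includes the size of each lesion and the total extent.
- "The estimates of size will then be compared with the results from histopathological examination, which is considered to be the reference standard".
- A treatment plan must exist at inclusion, "based on information obtained from findings at mammography, ultrasound, and core biopsy/cytology, according to current clinical standards". The routine imaging is therefore complete before CEM is performed.
- The CEM images are "read by at least two experienced radiologists in consensus, and with access to the images and results of routine clinical imaging".

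The article describes no CEM size recorded without that access. Nor does it define the size endpoint as the accuracy of CEM added to routine imaging.

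**The concern.** The endpoint is a head-to-head question about three modalities, but the three measurements are not made under comparable information. A CEM reader who is unsure of a lesion's edge can look at the mammography or ultrasound size and adjust. The routine sizes that supported the first plan were produced before CEM and could not be adjusted in return.

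When one estimate may borrow from the others, its error against histopathology can shrink even if the contrast images contribute little to sizing. A smaller Bland–Altman spread or a higher correlation for CEM would then be compatible with two explanations: CEM measures size better, or a reader with more information measures size better. The planned data cannot separate them. What is at stake is the sentence the trial would write on this endpoint, that CEM is more accurate for size than mammography and ultrasound.

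**Working it through.** **No planned figure to reproduce.** The article gives no sample size or target difference for the size endpoint. Its one calculation, 195 patients per arm, is for the primary endpoint and does not depend on how size is read.

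**Step 1: the sections side by side.**

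| Question | Where | Content |
|---|---|---|
| What is asked? | Secondary endpoints | CEM against mammography and ultrasound, with histopathology as reference |
| How is it analysed? | Statistical analyses | Each modality separately |
| When are mammography and ultrasound done? | Pre- and postoperative assessment | Before the first treatment plan, hence before CEM |
| What do CEM readers see? | Same section | The routine images and their results |

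The first two rows need a CEM size that stands on its own. The last two allow a CEM size informed by the other two modalities.

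**Step 2: can the feasibility data show how large the effect is?** Results of the feasibility study gives these differences from histopathology (units not stated):

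- CEM: "mean difference − 1.36, SD ± 18.45"
- mammography: mean −4.18, SD 26.20
- ultrasound: mean −8.36, SD 24.30

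As an illustration, suppose a reader simply averaged the mammography and ultrasound sizes and used no CEM information. With error correlation r,

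SD = ½ √(26.20² + 24.30² + 2r × 26.20 × 24.30) = ½ √(1276.93 + 1273.32 r)

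- r = 0: 17.9
- r = 0.5: 21.9
- r = 0.7: 23.3

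This equals the CEM value of 18.45 at r = (4 × 18.45² − 1276.93) / 1273.32 = 84.68 / 1273.32 = 0.07. Above that correlation, the average of the two is worse than the reported CEM figure.

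The mean also fails to match. Equal weights give (−4.18 − 8.36) / 2 = −6.27, and any weighted average of the two lies between −8.36 and −4.18. The CEM mean is −1.36.

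**Step 3: a milder illustration.** Suppose CEM alone were no better than ultrasound (SD 24.30), and the informed reading behaved like an equal average of all three, with common error correlation r:

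SD = ⅓ √(2 × 24.30² + 26.20² + 2r(2 × 24.30 × 26.20 + 24.30²)) = ⅓ √(1867.42 + 3727.62 r)

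- r = 0.3: 18.2
- r = 0.5: 20.4
- r = 0.7: 22.3
- r = 0.9: 24.1

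This falls to 18.45 or below only if r is at most (9 × 18.45² − 1867.42) / 3727.62 = 0.32.

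**Reading of steps 2 and 3.** Informed reading could lower the SD appreciably or hardly at all, depending on r and on how much readers lean on the routine sizes. The article gives neither, and it does not say how the feasibility images were read. The direction is plausible, but the size cannot be derived.

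**The case against.** **Informed reading is deliberate and fits the aim.** The article sets out to study the added value of CEM on top of standard imaging, and the CEM report goes to a second multidisciplinary conference where all imaging is considered. This stands for the clinical reading and for the primary endpoint. It does not rescue the size endpoint, which is worded and analysed modality by modality. Added value is a different question from which modality is more accurate.

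**No superiority test for size is named.** True, the plan is descriptive. But the endpoint asks which modality is better, and the description will be read as the answer.

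**Three stronger readings are tempting, and the document supports none of them.**

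- *The recorded CEM size is a composite of all imaging.* The article grants access; it does not say the sizes are combined. Readers may measure mainly on the contrast images, and the reporting forms, which are in additional files not at hand, may say so. Access creates the opportunity for borrowing and does not prove that it happens.
- *CEM also gains from consensus reading that the other modalities lack.* Averaging two readers with error correlation 0.3 to 0.7 would multiply the SD by √((1 + r)/2), that is 0.81 to 0.92. But the article does not say how many readers mammography or ultrasound had, and silence in a condensed article does not show single reading.
- *Most or all of the feasibility advantage comes from pooling.* Averaging mammography and ultrasound reaches the CEM SD only at near-zero error correlation. Errors of two methods measuring the same lesion against the same specimen are more likely to be positively correlated. Pooling the two also cannot give the CEM mean difference.

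**Which ultrasound size is analysed is not stated.** A second-look ultrasound may follow CEM when additional tumors are found. The one-way flow of information is therefore clear only for the routine ultrasound done before inclusion.

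**Conclusion.** The point holds in a limited form. As written, the plan compares CEM read with knowledge of mammography and ultrasound against each of those modalities, and so cannot support a conclusion about CEM alone. The comparison can favour CEM by an amount that is unknown and cannot be recovered afterwards from the planned data.

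This rests on the stated reading procedure, the stated endpoint and the stated analysis. It assumes only that readers with access to earlier sizes may use them. It does not rest on the feasibility SDs, which are illustrative, or on any difference in reader numbers. The primary endpoint and the sample size are unaffected; the consequence is confined to one secondary endpoint and how it is reported.

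**What to change.** **For patients still to be read.** Have the same readers enter and lock the CEM lesion size and total extent before opening the routine images and reports. They then open them and carry out the informed reading for the second multidisciplinary conference exactly as now. Use the locked sizes for the comparison with mammography and ultrasound. No extra readers or examinations are needed. The costs are a small added reading step and a locked field in the CEM form. Blinding is incomplete if a reader already knows the case from the work-up or the first conference.

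**For patients already read, or if the reading order stays.** Inclusion began in November 2020, so some examinations had presumably been read before the article appeared in October 2021. For these, state the endpoint and the conclusion as the accuracy of CEM read with knowledge of mammography and ultrasound (added value), not of CEM alone. This changes wording only and needs no new data.

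If both apply, report the two sets of patients separately. The cost is a smaller number for the comparison based on locked sizes.

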#### Data collection

Data will be collected from the study-specific questionnaire, the Breast-Q™ questionnaire, medical records, *Sectra IDS7* (the radiology information system, picture archive and communication system) and *LIMS* (laboratory information management system for histopathology reports) Data will be recorded in *REDCap* (a web-based application for electronic data capture in research studies) electronic case report forms (e-CRF) administered and monitored by *Clinical Studies Sweden – Forum South, Region Skåne.*

### Randomization

Web-based un-blinded simple randomization will be performed in *REDCap* by a randomization tool. Patients will be randomized 1:1 to either arm A, additional preoperative CEM or arm B, no further preoperative imaging. Randomization will be stratified between sites. All patients who fulfil the inclusion criteria will be registered in a screening log on-site.

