### Patient enrollment

Potential participants in this prospective multicenter trial will be identified at preoperative multidisciplinary team (MDT) conferences after diagnostic work-up of suspicious breast cancer detected by mammographic screening or clinical symptoms. The study will include 440 patients with strongly suspected or an established diagnosis of primary breast malignancy, for whom surgery is planned to involve either partial or total mastectomy based on mammography, ultrasound and core biopsy or cytological examinations. The participants will be randomized either to additional imaging with CEM or to no further preoperative imaging. The findings of CEM will be considered at a second MDT conference, at which changes may be made to the primary treatment plan. The inclusion and exclusion criteria are given in Table 1.

**Table 1 Tab1:** Inclusion and exclusion criteria

**Inclusion criteria**	Planned primary surgery for suspected or verified primary breast malignancy
	Age ≥ 18 years
	Signed informed consent
**Exclusion criteria**	Planned neoadjuvant therapy
	On-going pregnancy
	Iodinated contrast agent allergy
	Renal disease or abnormal S-creatinin (normal range 45–90 μmol/l)
	Untreated thyrotoxicosis (including multinodular goitre) (upon suspicion check P-thyrotropin level, exclusion if < 0.4 mIE/l)
	Severe heart failure
	Myastenia gravis
	Breast implant
	Local recurrence as index lesion
	Inability to understand oral or written information about the study

Study inclusion started in November 2020 and inclusion of the required number of participants is expected to take between two and 3 years depending on the ongoing pandemic of Covid-19. Patients diagnosed at the breast centers in Helsingborg, Kristianstad and Halmstad in Sweden, will be included.

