### Statistical methods

#### Power calculation

Based on the assumption that treatment planning will be modified in 18% of patients undergoing CEM, 195 patients will be needed in each arm to show that this proportion is significantly larger than a null proportion of 10%, using a power of 90% and an alpha value (two-sided) of 5%. We will recruit 220 patients per arm (440 patients in total) to account for a drop-out rate of approximately 10%.

The power calculation for the number of participants in this study is based partly on the result of the feasibility study, in which changes were made in the treatment plan in 10 out of 47 cases (21%) after CEM [21]. In previous studies, CEM and MRI have shown similar sensitivity and specificity in breast imaging. The results of the present study will thus also be compared with those of the POMB study in which preoperative MRI was used [13] resulting in changes in the treatment plan in 18% of cases.

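### Randomisation is called both simple and stratified by site: without a restriction within site, the stratification has no effect and 220 per arm is not fixed, though the consequence is modest

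*Protocol article*

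**What the plan says.** The Randomization section of the protocol article makes three statements on method:

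- Type: "Web-based un-blinded simple randomization will be performed", using the REDCap tool.
- Ratio: "Patients will be randomized 1:1 to either arm A, additional preoperative CEM or arm B, no further preoperative imaging".
- Site: "Randomization will be stratified between sites".

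No blocks, minimisation or other restriction is mentioned anywhere in the article.

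Two other places bear on this. Patient enrollment names three recruiting centres: "Patients diagnosed at the breast centers in Helsingborg, Kristianstad and Halmstad in Sweden, will be included". The Power calculation section sets a size for each arm: "195 patients will be needed in each arm", and then, to allow for about 10% drop-out, "We will recruit 220 patients per arm (440 patients in total").

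For comparisons between groups, the Statistical analyses section names Fisher's exact test, where applicable. It says nothing about site.

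**The concern.** Simple randomisation normally means unrestricted allocation: each patient is assigned independently with probability one half. Stratification by site is meant to keep the arms balanced within each site. It does so only when allocation within the site is restricted, for example by permuted blocks. The two statements therefore describe different schemes in ordinary usage, and a reader cannot tell which one is running.

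Two things depend on the answer. First, the size of the CEM arm. The power statement tests the proportion of changed plans in that arm against a fixed null, so primary power depends on how many patients the CEM arm contains. Second, balance by site. Reoperation, avoidable mastectomy, Breast-Q scores and costs are compared between arms and may vary with local practice. Site balance by design is the only control for site that the article describes, and under simple allocation it would be absent.

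**Working it through.** **1. The plan's own sample size.** The inputs from the Power calculation section are p1 = 0.18, p0 = 0.10, two-sided alpha 5% and power 90%. For a one-sample test of a proportion:

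n = [(1.960·√(0.10·0.90) + 1.2816·√(0.18·0.82)) / 0.08]² = 182.4

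With continuity correction: n/4 · [1 + √(1 + 2/(n·0.08))]² = 194.7, rounded up to 195. This reproduces the stated figure. Allowing for drop-out, 195/0.9 = 217, which the plan rounds up to 220. The test uses the CEM arm only.

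**2. Does stratifying a simple scheme change anything?** Suppose each site has its own list of independent 1:1 assignments. Every patient still has probability one half, independently of all others. The number in the CEM arm is Binomial(440, 0.5) overall and Binomial(n, 0.5) at a site with n patients. A single list covering all sites gives the same distributions.

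**3. Arm size under simple allocation of 440.**

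- 95% range for one arm: 199 to 241.
- Probability of exactly 220/220: 3.8%.
- Probability of an arm difference of 44 or more: about 4%.

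**4. Balance at a site.** The article gives no recruitment by site. Assuming equal recruitment, 440/3 is about 147 per site:

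- 95% range for one arm: 62 to 85.
- Probability of an arm difference of at least 10% of the site's patients: about 25%.

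**5. Evaluable patients in the CEM arm, with 10% drop-out.** The evaluable number is Binomial(440, 0.45) under simple allocation and Binomial(220, 0.9) with a fixed 220. The chance of fewer than 195 is 0.369 and 0.212 respectively.

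**6. Power of the plan's own test.** For m evaluable patients, with continuity correction:

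power = Φ{[0.08 − 1/(2m) − 1.960·√(0.09/m)] / √(0.1476/m)}

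| CEM arm | Evaluable (90%) | Power |
|---|---|---|
| 199 | 179 | 87.7% |
| 220 | 198 | 90.4% |
| 241 | 217 | 92.6% |

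Averaged over the distributions in step 5, expected power is 90.35% under simple allocation and 90.43% with a fixed 220.

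**7. Efficiency of a two-arm comparison.** A 199/241 split keeps 4·199·241/440² = 0.991 of the efficiency of equal arms.

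**The case against.** The strongest reply is that this is loose wording in a condensed article. The stratification sentence and the planned 220 per arm both suggest a restricted scheme, and 'simple' may not be meant technically. Block sizes and list construction are properly left to the full protocol. That is fair, and the point does not rest on their absence. It rests on two positive statements, one of which is either wrong or without effect.

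Unrestricted allocation is also a defensible choice at this size. It is the least predictable scheme, which matters in an un-blinded trial at three sites, and steps 6 and 7 show that it costs very little. This stands, and it limits the weight of the point.

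Three stronger readings might be inferred, and the documents do not support them:

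- *That the two statements are logically incompatible.* They are not. Simple lists by site can exist, but they achieve nothing.
- *That the primary test has a 37% chance of being underpowered.* The 0.369 is the chance of fewer than 195 evaluable patients, and it is already 0.212 with a fixed 220. Power changes gradually around 195, and the CEM arm is as likely to exceed 220 as to fall short of it.
- *That site confounds the between-arm results.* Imbalance arising by chance under valid randomisation is not systematic confounding. It introduces no bias, and the type I error is kept.

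**Conclusion.** The point holds as a contradiction in the description of the allocation method, with modest consequences. As written, either the word 'simple' is wrong or the stratification is ineffective, and in the second case 220 per arm is an expectation with a 95% range of 199 to 241. The required sample size of 195 is unaffected. Expected primary power differs by less than 0.1 percentage point, and at the low end of the range (199 in the CEM arm, 179 evaluable) it is about 87.7%.

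These figures assume truly independent 1:1 allocation, 10% drop-out and the one-sample test that reproduces the plan's 195. The site range of 62 to 85 also assumes equal recruitment at the three centres. Which scheme REDCap actually runs cannot be established from the article.

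**What to change.** State the scheme that REDCap runs.

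- *If allocation is restricted within site:* delete 'simple', describe it as site-stratified restricted randomisation, and say that block sizes, if blocks are used, are concealed from the sites.
- *If allocation is truly simple:* withdraw the stratification sentence and give 440 as the total, with 220 per arm as the expected and not the fixed number.

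In either case, account for site in the between-arm comparisons of secondary endpoints, and do not rely only on an unstratified Fisher's exact test. A site-stratified exact or Mantel-Haenszel test would serve for binary endpoints, or site can enter a model as a covariate. If the analysis plan, which is not shown, already does this, nothing more is needed there.

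The cost is a sentence or two of text and slightly more analysis work. Replacing a running allocation list mid-trial is not required: the gain in expected power would be negligible, and blocks would make upcoming allocations somewhat easier to guess in an un-blinded trial.
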